### Sample size

#### Primary outcome: adherence to the guidelines for antimicrobial prescribing in primary care in Ireland (control - intervention arm a)

Previous research has established that 56% of UTI patients receive an antimicrobial, with only 38% of prescriptions made out for the recommended first-line treatment
[8]. Sample size calculations are based on an absolute 10% increase in first-line prescriptions according to guidelines (primary outcome).

Additional assumptions for sample size calculations are:

• Power of 80% and *α* of 5%.

• Practice attrition is dependent on the completeness of consultation coding, which will be monitored and corrected during Phase 1.

• Patient attrition will be close to 0%, as all coded consultations will be included.

• Improvement in the control group due to participation in the coding workshops has been anticipated.

• An intracluster correlation (ICC) of 1% was obtained from a previous study in this area
[6,12].

A total sample size of 920 patients recruited from 20 practices gives a power of 80% to detect a significant change in the proportion of patients to receive first-line antimicrobial when treated for UTI when the ICC is 1%.

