#### The control arm

To gather comparable data on UTI consultations, practices in the control arm will complete a coding workshop at the beginning of Phase 1. For the remainder of the intervention, the control arm will provide 'usual care’ and will receive their audit and feedback reports at the end of intervention Phase 3. Practices in the control arm will also submit urine samples from UTI patients and request patients’ mobile telephone numbers for the duration of the intervention.

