### Method of quantitative data analysis

Quantitative analysis will be undertaken using SPSS for Windows release 20.0 (SPSS Inc., Chicago, IL, USA) and Stata 11 (Stata Corporation, Texas). Multilevel analysis will be performed using MLwiN version 2.21 software and cost-effectiveness analysis will be conducted using Excel and Stata 11. Statistical significance will be set at the 5% level for all outcomes.

Multivariate analysis will examine intervention and control arm changes from baseline measures and will follow the principle of intention to treat. Outcomes will be compared between intervention (arms A and B) and the control arm, using a multilevel logistic modelling approach to control for baseline prescribing as well as other confounding variables at patient and practice level. All statistical analysis will be undertaken in accordance with current guidelines for randomized controlled trials
[71].

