### Limitations of the study

The method of data collection used requires a coding workshop to improve routine consultation coding for UTIs in all practices participating in the intervention, including those in the control group. The inclusion of the control group in the coding workshop may affect the outcome; however antimicrobial treatment was not discussed at these workshops. To limit this bias, researchers delivering the workshops were blinded as to randomization of practices to intervention and control. This bias is anticipated to increase awareness in the control group, resulting in a potentially smaller difference between intervention and control arms.

Computerized remote data extraction will be used to assess differences between the intervention and control arms. Data analysis will not be blinded. However, as the outcome is an absolute comparison in first-line prescriptions of antibiotics, before and after the intervention, the risk of bias is minimal.

The use of patient mobile telephone numbers for evaluation purposes, while novel and direct, introduces selection bias, owing to different levels of mobile phone penetration and familiarization with their use. For research evaluation purposes, however, the implementation of follow-up by mobile telephone technology allows evaluation of consumption (and thereby the impact of delayed prescribing) rather than simply the evaluation of prescribing behaviour by GPs. However, since the sample can be related back to the source population and the selection bias can be estimated, the final evaluation can be considered within this context.

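### The sample size section lists control-arm improvement as an assumption, but 920 patients and 80% power contain no allowance for it

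*Protocol article*

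**What the plan says.** The primary sample size section of the Protocol article covers control v intervention arm A. It takes its control rate from earlier research, in which "only 38% of prescriptions made out for the recommended first-line treatment". It then states that "Sample size calculations are based on an absolute 10% increase in first-line prescriptions according to guidelines (primary outcome"). Its additional assumptions include 80% power, a 5% alpha, an ICC of 1%, patient attrition near zero, and this line: "Improvement in the control group due to participation in the coding workshops has been anticipated". The result is 920 patients from 20 practices for 80% power. The line on control improvement has no size, and the section gives no other control rate and no reduced effect.

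The section on the control arm explains where the improvement would come from: "practices in the control arm will complete a coding workshop at the beginning of Phase 1". The limitations section gives the expected direction: "This bias is anticipated to increase awareness in the control group, resulting in a potentially smaller difference between intervention and control arms".

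On the test itself, the analysis methods section says only that "Statistical significance will be set at the 5% level for all outcomes". Neither section says whether the test is one- or two-sided. The feasibility section projects 2,038 treated patients from 20 practices over the six months.

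**The concern.** An item listed as a sample size assumption should show up in the sample size. Here the protocol predicts that its control arm will move and its primary contrast may shrink, yet the printed number seems to rest on the historical control rate and the full 10 points.

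If so, the 80% describes a comparison with practices as they were before the trial. The trial will actually compare arm A with practices that have had a coding workshop. Should the net difference fall below 10 points, the stated power does not apply, and a null primary result would be harder to interpret than the protocol suggests.

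**Working it through.** **Inputs.** From the primary sample size section: control 38%, arm A 48%, alpha 5%, ICC 0.01, 920 patients, 20 practices. From the feasibility section: 2,038 treated patients in 20 practices. Assumed: equal allocation (10 v 10 practices), equal cluster sizes, and a control gain of 1 to 3 points, because no size is given.

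**Formulas.** Patients per practice m = N/20. Design effect DE = 1 + (m − 1) × 0.01. Effective n per arm = (N/2)/DE. SE = √{[p₁(1 − p₁) + p₂(1 − p₂)]/n}. Power = Φ((p₂ − p₁)/SE − z), with z = 1.960 two-sided or 1.645 one-sided.

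**Step 1: reproduce the plan's figure.**
- m = 920/20 = 46; DE = 1 + 45 × 0.01 = 1.45; n = 460/1.45 = 317.2 per arm.
- SE = √[(0.2356 + 0.2496)/317.2] = 0.0391; 0.10/0.0391 = 2.557.
- Two-sided: Φ(2.557 − 1.960) = 72.5%.
- One-sided: Φ(2.557 − 1.645) = 81.9%.
- If the 20 practices were per arm: m = 23, DE = 1.22, n = 377.0, two-sided power 79.6%.

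The stated 80% is therefore approached in two ways: one-sided with 20 practices in total, or two-sided with 20 per arm. Both use the unadjusted 38% v 48%.

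**Step 2: is there room for an allowance?** With 920 patients and 20 practices, the difference from 38% detectable at 80% power is 10.96 points two-sided, more than the whole target. One-sided it is about 9.7 points, which leaves roughly 0.3 points. Neither holds a meaningful control gain.

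**Step 3: the gain is shared equally.** At 40% v 50% and N = 920, two-sided power is 72.1% against 72.5%. A shared gain changes power by less than one point.

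**Step 4: control gains and arm A stays at 48%.**

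| Control v arm A | Net difference | 920, two-sided | 920, one-sided | 2,038, two-sided |
|---|---|---|---|---|
| 38% v 48% | 10 | 72.5% | 81.9% | 89.9% |
| 39% v 48% | 9 | 63.2% | 74.3% | 82.7% |
| 40% v 48% | 8 | 53.0% | 65.2% | 73.1% |
| 41% v 48% | 7 | 42.8% | 55.3% | 61.4% |

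For 2,038: m = 101.9, DE = 2.009, n = 1,019/2.009 = 507.2 per arm.

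Pooled-variance formulas give results within about half a point (for example 72.1% and 89.7% in the first row). The normal approximation is somewhat favourable with so few clusters: a t reference on 18 degrees of freedom gives 67.7% in place of 72.5%.

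**The case against.** The strongest reply is that the coding workshop goes to every practice. The intervention components table assigns it to all arms, and the workshop section says the same. Urine submission and the request for mobile numbers also apply in the intervention arms. A gain from these activities could therefore raise both arms together, and Step 3 shows that this would cost almost nothing. That stands, and it limits the point. A reader might infer from the table in Step 4 that a 2 to 3 point rise in control simply costs the trial 17 to 30 points of power. The documents do not support that: the 2 to 3 points are assumed, and the loss follows only if arm A fails to share the gain.

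The planned analysis helps too. Under the implementation section, baseline data are collected in the two months after the coding workshop, and the multilevel model controls for baseline prescribing. A workshop effect already present in Phase 1 is then in the baseline of both arms. The simple two-proportion calculation ignores this, and the document gives no figure from which to quantify the benefit.

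The word anticipated might also mean that the 10 points are already net of control improvement. That reading is open, but the section does not say so. It would require arm A to exceed 48%, which is stated nowhere. Even then, 920 patients from 20 practices give only about 72% power two-sided.

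Finally, the limitations section discloses the issue and adds that antimicrobial treatment was not discussed at the workshops. This makes a large gain less likely. It does not put an allowance into the calculation, and the same section still expects a possibly smaller difference.

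**Conclusion.** The point holds in a limited form. The protocol names control improvement as a sizing assumption and expects it to narrow the contrast, but 920 patients and 80% power carry no allowance for it. This does not depend on any assumed gain: it follows from Steps 1 and 2 under either sidedness.

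The consequence is conditional. It is negligible if both arms gain equally. If the net difference is 9, 8 or 7 points, two-sided power is about 63%, 53% and 43% at 920, and about 83%, 73% and 61% at 2,038. Which of these applies cannot be settled from the document. The projected 2,038 softens the problem considerably, giving about 90% for a full 10-point net difference.

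The figures rest on 10 v 10 practices, equal cluster sizes, an ICC of 1% and an unadjusted comparison. It would go too far to say that the trial is bound to lose a particular amount of power, or that the comparison is invalid.

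**What to change.** In the primary sample size section:

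1. Replace the line on control improvement with a statement that the power refers to a 10-point net difference between arm A and a control arm that has had the coding workshop.
2. State whether the 5% test is one- or two-sided.
3. Restate the power for 920 patients from 20 practices (about 72% if two-sided) and for the projected 2,038 (about 90%).
4. Beside it, show the power for net differences of 7, 8 and 9 points, labelled as a sensitivity that applies only to the extent that control gains and arm A does not.

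The cost is a few sentences and one small table. The stated power becomes less favourable; no extra patients or practices are needed.

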### Feasibility

According to the most recent laboratory urine sample submission (personal communication, 2012), an average of 364 urine samples (median 257, range 25 to 1,162) per year per eligible practice are sent in to the GUH laboratory. Considering that the intervention will run over a six-month period (Phases 2 and 3) and without any adjustment for the total number of UTI-related consultations, an estimated 3,640 urine samples will be submitted from 20 participating practices during this period. If 56% of these patients are prescribed an antimicrobial over a six-month period, a total of 2,038 patients will be prescribed an antimicrobial.

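### The 80% power claimed for 920 patients in 20 practices makes no allowance for unequal practice size, although the protocol's own volumes range from 25 to 1,162 a year; this costs about 4 to 8 further points of power

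*Protocol article*

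**What the plan says.** The sample-size section for the primary outcome (control against arm A) concludes: "A total sample size of 920 patients recruited from 20 practices gives a power of 80% to detect a significant change", at an ICC of 1%. Its inputs are "Power of 80% and *α* of 5"%, a starting level described as "with only 38% of prescriptions made out for the recommended first-line treatment", and this effect: "Sample size calculations are based on an absolute 10% increase in first-line prescriptions according to guidelines (primary outcome". The ICC is sourced as follows: "An intracluster correlation (ICC) of 1% was obtained from a previous study in this area". On inclusion it says: "Patient attrition will be close to 0%, as all coded consultations will be included". Neither this section nor the analysis section ("Statistical significance will be set at the 5% level for all outcomes") says whether the test is one- or two-sided. None of the listed assumptions concerns how much practices differ in size.

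The Feasibility section that follows gives laboratory volumes: "an average of 364 urine samples (median 257, range 25 to 1,162) per year per eligible practice". It multiplies the average up to 2,038 prescribed patients from 20 practices in six months. The method of quantitative data analysis is a multilevel logistic model.

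**The concern.** A total N, a number of practices and an ICC, with nothing more, imply a common cluster size of 920/20 = 46. The design cannot deliver that. All coded consultations enter, so each practice contributes in proportion to its volume, and the largest eligible practice submits 1,162/25 = 46 times as many samples as the smallest. A mean well above the median shows strong right skew.

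With a positive ICC, extra patients in an already large practice add little information, and a small practice contributes little in any case. Unequal sizes therefore lower the effective sample size below the equal-cluster figure. This is separate from whether 920 follows from the printed inputs: an N corrected to give 80% with equal practices would still miss 80% with practices of these sizes.

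**Working it through.** **Inputs.** p1 = 0.38, p2 = 0.48, ICC = 0.01, N = 920 and 20 practices come from the sample-size section. I take 10 practices per arm and a two-sided 5% test.

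**The plan's own figure.** With equal practices the design effect is 1 + (46 − 1) × 0.01 = 1.45, so the effective n per arm is 460/1.45 = 317.2. Power = Φ{[0.10√n − 1.96√(2 × 0.43 × 0.57)] / √(0.38 × 0.62 + 0.48 × 0.52)} = Φ{[1.781 − 1.372]/0.697} = Φ(0.587) = 72.1%. The stated 80% is not reproduced two-sided. A one-sided 5% test gives 81.7%, which is near the claim, but only with equal practices. So no allowance for unequal size can be contained in 920.

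**CV of practice size.** The protocol gives no standard deviation, so the CV must be inferred:

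- Range/4: (1,162 − 25)/4 = 284; 284/364 = 0.78.
- Lognormal with mean 364 and median 257: CV² = (364/257)² − 1 = 1.006, so CV is about 1.0.
- Distributions bounded at 25 and 1,162 and matched to mean and median: 0.86 (truncated lognormal) and 0.89 (scaled beta).

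**Planning formula.** Design effect = 1 + ((1 + CV²) × 46 − 1) × 0.01. At CV 0.78 this is 1.730, effective n = 460/1.730 = 265.9, and power = 64.5%.

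| CV | Design effect | Effective n per arm | Power, two-sided | Power, one-sided |
|---|---|---|---|---|
| 0 | 1.450 | 317.2 | 72.1% | 81.7% |
| 0.6 | 1.616 | 284.7 | 67.5% | 77.9% |
| 0.78 | 1.730 | 265.9 | 64.5% | 75.4% |
| 0.9 | 1.823 | 252.4 | 62.2% | 73.5% |
| 1.0 | 1.910 | 240.8 | 60.2% | 71.7% |

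**Efficient weighting, closer to the planned multilevel model.** A practice with m patients carries information m/(1 + (m − 1) × 0.01). Scale volumes so that the mean is 46 (46/364 = 0.126). The largest practice then has about 147 patients and contributes 147/2.46, about 60. An average practice contributes 46/1.45, about 32. So 3.2 times the patients bring only 1.9 times the information. Twenty sizes were simulated from lognormal and gamma distributions, clipped to 25 to 1,162, scaled to each N and split 10 against 10:

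| N | Equal sizes | Nominal CV 0.78 | Nominal CV 1.0 |
|---|---|---|---|
| 920 | 72.1% | 66.9% to 68.0% | 64.5% to 66.4% |
| 1,240 | 80.2% | 74.9% to 76.0% | 72.3% to 74.5% |
| 2,038 | 89.7% | 85.3% to 86.3% | 82.9% to 85.0% |

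At 920 the loss is 72.1 − 68.0 = 4.1 to 72.1 − 64.5 = 7.6 points.

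**N for 80% power with 20 practices, two-sided.** About 1,232 with equal sizes. With efficient weighting, roughly 1,480 to 1,580 covers CV 0.78 and the lognormal case at CV 1.0; the gamma case at CV 1.0 gives 78% at 1,580 and so needs somewhat more. The planning formula needs 1,588 at CV 0.6 and about 1,980 at CV 0.78.

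**The case against.** The strongest reply is that 920 is a minimum, not a stopping point. The protocol expects 2,038 prescribed patients, and at that yield efficient weighting keeps power at about 83% to 86% even with unequal practices. This stands, and it limits the practical harm. It does not rescue the printed statement, which attaches 80% to 920. It also shows that the apparent twofold surplus is much smaller: under the planning formula, 2,038 gives 80.4% at CV 0.78 and 74.7% at CV 1.0.

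The drop from 80% to 72% at 920 has nothing to do with unequal size, so only the further 4 to 8 points belong to this issue. That is correct, and the two shortfalls are kept apart above. The planning formula is also conservative for a multilevel model, so the upper figure of about 2,000 overstates what the planned analysis needs; about 1,500 to 1,600 is the more coherent target.

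The CV is inferred, and from urine samples in all eligible practices, not prescribed patients in the 20 analysed. The realised value could be lower or higher. The protocol uses the same proxy for its own yield, however, and the direction of the error does not depend on the exact CV.

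Finally, adjustment for baseline prescribing could reduce the between-practice variance. If it halved the ICC to 0.5% (an assumption), 920 would give about 79% with equal sizes and 75% to 77% with unequal ones. The sizing claims no such gain, and 80% would still be missed.

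**Conclusion.** The concern holds. The statement that 920 patients in 20 practices give 80% power rests on equal practice sizes, which the protocol's own volumes contradict. Unequal size costs about 4 to 8 points at 920 under efficient weighting (72% to between 64% and 68%) and about 8 to 12 under the planning formula at the same CVs (to between 60% and 65%). A one-sided reading does not save the claim: 81.7% falls to about 75% at CV 0.78. Nor does correcting only the equal-cluster arithmetic, since 1,240 patients then give 72% to 76% under efficient weighting.

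These figures assume 10 practices per arm, ICC 1%, no gain from baseline adjustment and a CV of about 0.78 to 1.0 before clipping to the published range. If the expected 2,038 patients are reached, the primary comparison probably keeps at least 80% power under the multilevel analysis. The fault therefore lies in the stated justification and its margin and does not make the trial unworkable.

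**What to change.** Recompute the primary sample size with an explicit CV of practice size, taken from the laboratory volumes of the 20 practices in this comparison. The protocol prints only summary figures, so if the individual volumes are not to hand they should be requested from the laboratory; failing that, use a range of CVs. Either the design effect 1 + ((1 + CV²)m − 1) × ICC or the sum of m_i/(1 + (m_i − 1) × ICC) per arm will serve; say which, because the first is the more conservative. State whether the test is one- or two-sided.

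Then replace the claim of 80% at 920 with the result. On the published distribution this is roughly 1,500 to 1,600 prescribed patients for 80% under multilevel weighting, and up to about 2,000 under the planning formula at CV 0.78; equivalently, power at 920 is about 65%. Both figures also include the separate equal-cluster shortfall. Report beside it the power at the expected six-month yield with the same unequal sizes.

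The cost is one recalculation and a less favourable power statement. No extra practices are needed for this correction, and the analysis does not change.

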**Methods/design:**

The Supporting the Improvement and Management of Prescribing for urinary tract infections (SIMPle) study is a three-armed intervention with practice-level randomization. Adult patients presenting with suspected UTIs in primary care will be included in the study.

The intervention integrates components for both GPs and patients. For GPs the intervention includes interactive workshops, audit and feedback reports and automated electronic prompts summarizing recommended first-line antimicrobial treatment and, for one intervention arm, a recommendation to consider delayed antimicrobial treatment. For patients, multimedia applications and information leaflets are included. Thirty practices will be recruited to the study; laboratory data indicate that 2,038 patients will be prescribed an antimicrobial in the study. The primary outcome is a change in prescribing of first-line antimicrobials for UTIs in accordance with the Guidelines for Antimicrobial Prescribing in Primary Care in Ireland. The study will take place over 15 months with a six-month intervention period. Data will be collected through a remote electronic anonymized data-extraction system, a text-messaging system and GP and patient interviews and surveys. The intervention will be strengthened by the implementation of a social marketing framework and an economic evaluation.

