#### Secondary outcome: decrease in the quantity of consumption (control - intervention arm B)

To estimate the potential power to detect this secondary outcome, an additional sample size calculation was carried out.

• 56% of the patients presenting with a UTI, and for whom a urine sample was submitted for microbiological analysis, received a prescription
[8].

• A 20% decrease in consumption can be achieved through delayed prescribing
[42].

Taking account of the cluster effect and based on previous ICC estimates, a total sample size of 240 patients recruited from 20 practices gives a power of 80% to detect a significant change in the proportion of patients who reduce antimicrobial consumption through delayed prescribing if the ICC is 1%.

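### At two-sided 5%, the protocol's own inputs give about 72% power at 920 patients, not 80%; 80% needs about 1,240, which is fewer than the 2,038 it projects

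*Protocol article*

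**What the plan says.** All the relevant material is in the Protocol article.

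- **Sample size, primary outcome (control versus arm A).** The calculation uses a first-line share of 38% of prescriptions, an absolute rise of 10 percentage points, 80% power, alpha 5%, an intracluster correlation (ICC) of 1% and patient attrition near zero. It concludes: "A total sample size of 920 patients recruited from 20 practices gives a power of 80% to detect a significant change". The same list of assumptions notes: "Improvement in the control group due to participation in the coding workshops has been anticipated".
- **Sample size, secondary outcome (control versus arm B).** For a fall from 56% by 20%, "a total sample size of 240 patients recruited from 20 practices gives a power of 80" per cent, again with an ICC of 1%.
- **Feasibility.** Laboratory data show "an average of 364 urine samples (median 257, range 25 to 1,162) per year per eligible practice". Over six months, 20 practices are expected to yield 3,640 samples and, at 56% treated, 2,038 treated patients.
- **Abstract, Methods/design.** "Thirty practices will be recruited to the study; laboratory data indicate that 2,038 patients will be prescribed an antimicrobial in the study".
- **Method of quantitative data analysis.** "Statistical significance will be set at the 5% level for all outcomes". Neither this section nor the sample size section says whether tests are one- or two-sided.

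**The concern.** The article prints both the inputs and the result of its primary calculation, so a reader can check one against the other. At the conventional two-sided level they do not agree: 920 is about a quarter below the number that the inputs require (920/1,240 = 0.74).

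The power statement is what readers use to judge how informative a null primary result would be. If the treated sample came in near 920, a null result would be credited with 80% power when the design had about 72%. The article also leaves unsaid what power the trial has at the number it actually expects, which is the more useful figure.

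The abstract adds a smaller error by pairing the expected yield of 20 practices with the recruitment figure of 30.

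**Working it through.** **Inputs.** p1 = 0.38, p2 = 0.48, power 80%, alpha 5%, ICC = 0.01, 20 practices and N = 920 all come from the sample size section. Two assumptions are added. Alpha is two-sided. There are 10 practices per arm, from 30 practices in three arms with equal allocation; Feasibility also uses 20 practices for its projection.

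**Power at the stated 920.**
- Patients per practice: m = 920/20 = 46.
- Design effect: 1 + (46 − 1) × 0.01 = 1.45.
- Effective sample per arm: 460/1.45 = 317.
- z = [0.10 × √317.2 − 1.960 × √(2 × 0.43 × 0.57)] / √(0.38 × 0.62 + 0.48 × 0.52) = (1.781 − 1.372)/0.697 = 0.587.
- Power = Φ(0.587) = **72.1%**. Unpooled and arcsine versions give 72.5% and 72.2%; a t reference on 18 degrees of freedom gives 67.7%.

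**Number needed for 80%.**
- Independent patients per arm: (1.960 × 0.700 + 0.8416 × 0.697)²/0.10² = 383.6, so 384.
- With k = 10 practices per arm fixed: m = n(1 − ICC)/(k − n × ICC) = 384 × 0.99/(10 − 3.84) = 61.7, so 62 per practice.
- Total: 20 × 62 = **1,240**. Check: design effect 1.61, effective 385 per arm, power 80.2%.

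**One-sided alternative.** At one-sided 5%, 920 gives 81.7%. The companion figure of 240 tests that reading. With 56% versus 36%, m = 12, the design effect is 1.11 and the effective sample is 108 per arm. Power is then 84% two-sided and 91% one-sided. The two-sided requirement is 213 (220 in whole patients per practice), or 237 (240) with continuity correction. The one-sided requirements are only 163 (180) and 186 (200).

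**Possible source of 920 (inference only).** If the number of practices, 20, was used as the cluster size, the design effect is 1 + 19 × 0.01 = 1.19. Then 768 × 1.19 = 914, which rounds up to 46 per practice, or 920. The same two-sided route gives 194 × 1.19 = 231, which rounds up to 12 per practice, or 240. The result above does not depend on this.

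**Power at the projected 2,038.** m = 101.9, design effect 2.009, effective 507 per arm, power 89.7% with equal practices. For unequal practices, DE = 1 + [(1 + CV²)m − 1] × ICC, where CV is the coefficient of variation of practice size. The CV is an assumption. Range/4 over the mean gives (1,162 − 25)/4/364 = 0.78; a lognormal fit to the mean of 364 and median of 257 gives about 1.0.

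| CV | power at 920 | power at 2,038 |
|---|---|---|
| 0 | 72% | 90% |
| 0.6 | 67% | 84% |
| 0.8 | 64% | 80% |
| 1.0 | 60% | 75% |

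**Abstract figure.** 364 × 0.5 × 20 × 0.56 = 2,038. For 30 practices, 364 × 0.5 × 30 × 0.56 = 3,058.

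**The case against.** **Sidedness is not stated.** This is the strongest defence, since a one-sided 5% test brings 920 to 81.7%. It means the finding must be worded as conditional on a two-sided test. It does not rescue the figure. The article declares no one-sided test, its wording is non-directional ("gives a power of 80% to detect a significant change in the proportion of patients to receive first-line antimicrobial"), and 240 fits two-sided calculations while carrying 91% power if one-sided.

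**Twenty practices per arm.** Reading 20 as per arm gives 79.3%, but that conflicts with 30 practices in three arms and with the Feasibility section.

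**The expected sample is larger.** All coded consultations are to be included, and 2,038 treated patients are projected from the same 20 practices. This stands, and it limits the consequence. A reader might infer that 920 is the target against which accrual will be judged, but nothing in the article ties a recruitment stop, data cut or adequacy check to it.

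**Other influences on power.** The planned adjustment for baseline prescribing could recover some power, although it is not an input to the stated calculation. Control-arm improvement could cost some: with control at 40% and arm A still at 48%, power at 920 would be 53%. That is only a sensitivity figure. The 10 points may already be net of the anticipated improvement, and if both arms move up by two points power stays at about 72%. The CV range likewise rests on urine samples across eligible practices, not treated patients in enrolled ones.

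**Conclusion.** The statement that 920 patients from 20 practices give 80% power is wrong on the protocol's own inputs at two-sided 5%: power is about 72%, and 80% needs about 1,240. This rests on the two-sided reading, equal allocation of practices and, for those two figures, equal practice sizes. The abstract's pairing of 2,038 with thirty practices contradicts the Feasibility section.

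A reader might go further and conclude that the trial is underpowered. The documents do not support that. The projected 2,038 exceeds 1,240, giving about 90% power with equal practices and about 80% at an assumed CV of 0.8; only towards a CV of 1.0 does it fall to about 75%. Nor do the documents show that 920 was computed for a different outcome, such as first-line treatment among all patients with a urinary tract infection.

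This should be fixed because the published justification is incorrect, but it does not threaten the design if the projected accrual is reached.

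**What to change.** In the sample size section:
- State that alpha is two-sided.
- Either restate the power at 920 as about 72%, or replace 920 with about 1,240 as the number needed for 80%.
- Add the power at the projected 2,038, allowing for unequal practices and using the actual laboratory volumes of the enrolled practices. Until those are used, quote about 90% with equal sizes and about 84% to 75% for assumed CVs of 0.6 to 1.0.
- Say whether the 10 points are net of the anticipated control-arm improvement.

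In the abstract, label 2,038 as the yield of the 20 practices in the primary comparison, or give about 3,058 for all 30.

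The cost is a text correction and one short recalculation. No extra recruitment follows, because all coded consultations are already included.
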